### Data collection, management and monitoring

Data collection and entry will be conducted by two independent researchers who are not involved in randomization, treatment, or evaluation. To ensure consistency, both researchers will independently enter the data and perform data validation, thereby ensuring the accuracy and completeness of the data. Participant data will be de-identified and access to identifiable information will be restricted to authorized study personnel only. Additionally, all research data will be reviewed by the Data Security Management Committee to monitor trial compliance and safety.

### Statistical methods

#### Sample size

The treatment response rate at week 4 serves as the primary outcome (23). A bilateral significance level (α) of 0.05 and a statistical power (1-β) of 0.9 were established. Based on our unpublished pilot data, in which the study design, intervention protocol, control condition, and outcome definition were highly consistent with the present trial, the treatment response rate for AA group at week 4 is anticipated to be 40.00%, while the NAA group is 22.22%. Using PASS 15.0 software, the required sample size was calculated to be N1 = N2 = 137 for both groups. Accounting for a 15% dropout rate, a total of 162 patients will be recruited in each group, resulting in an overall total of 324 patients.

### Statistical analysis

This study will utilize three databases: the Full Analysis Set, the Per-Protocol Set, and the Safety Set. Statistical analyses will be performed using SAS 9.4 software (SAS Institute Inc., Cary, North Carolina, USA). Continuous variables will be reported as mean and standard deviation or median (interquartile range), while categorical variables will be expressed as frequency (proportional composition). A *P*-value <0.05 will be considered statistically significant.

The primary outcome, the treatment response rate at week 4, will be compared using the Cochran-Mantel-Haenszel test. Secondary outcomes, including treatment response rate, treatment remission rate, and emergency medication usage, will be analyzed as qualitative data with repeated measures using generalized estimating equations. Changes in TST, SOL, SA, WASO, EMA, ADA, and SE as well as changes in ISI, GAD-7, PHQ-9, and QLQ-C30 scores, will be analyzed as quantitative data using mixed-effects models. Secondary outcomes will be considered supportive and exploratory, thus no formal adjustment for multiple comparisons will be applied. The incidence of adverse events will be analyzed using chi-square tests or Fisher’s exact tests. Missing data will be handled using mixed-effects models under the missing-at-random assumption. Multiple imputation will be performed as a sensitivity analysis to assess the robustness of the primary results. Key clinical and treatment-related variables, including study center, TNM stage, cancer treatment modalities, pain level, menopausal status, baseline ISI severity, and emergency medication usage, will be considered as pre-specified covariates where appropriate.

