## Methods

### Study design

This study will be conducted across three centers, including LongHua Hospital, Shanghai University of Traditional Chinese Medicine; Zhongshan Hospital, Fudan University; and Huashan Hospital, Fudan University. A total of 324 patients will be recruited and randomly assigned in a 1:1 ratio to either the AA group or the NAA group. Both groups will undergo a 4-week treatment, followed by a 12-week follow-up. **Figure 1** illustrates the flowchart of the trial, and **Table 1** presents a schematic timeline outlining the recruitment process, intervention schedule, and efficacy evaluations. The protocol for this study was based on the Standard Protocol Items: Recommendations for Intervention Trials (SPIRIT) 2013, as outlined in **Supplementary Material 1**.

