#### Secondary outcome

The secondary outcomes include the following eight indicators:

Treatment remission rate: The percentage of patients achieving an ISI score <8 at weeks 2, 4, 8, and 16.Treatment response rate at weeks 2, 8, and 16.Sleep diary (19): Total sleep time (TST), sleep onset latency (SOL), number of sleep awakenings (SA), wake after sleep onset (WASO), early morning awakenings (EMA), average duration of awakenings (ADA), and sleep efficiency (SE), as recorded in sleep diaries at weeks 0, 1, 2, 3, and 4.Change in ISI score: This will be evaluated at weeks 2, 4, 8, and 16.Generalized Anxiety Disorder-7 (GAD-7) (20): This scale assesses anxiety symptoms experienced by patients in the past two weeks. Evaluations will be conducted at Weeks 0 and 4.Patient Health Questionnaire-9 (PHQ-9) (21): This scale evaluates depression symptoms in the past two weeks. Evaluations will take place at Weeks 0 and 4.Quality of Life Questionnaire-Core 30 (QLQ-C30) (22): This 30-item scale assesses the quality of life among cancer patients across six dimensions and is widely used in clinical research. Assessment will be conducted at Weeks 0 and 4.Emergency medication usage: The percentage of patients using emergency medication usage, as well as the dosage, frequency, and duration of medication use, will be recorded at weeks 1, 2, 3, 4, 8, and 16.

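### GAD-7, PHQ-9, QLQ-C30 and the sleep-diary variables are analysed as changes with no own baseline among the named covariates; for the three week-0/week-4 scales, a mixed model of change cannot deliver the stated missing-data handling

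*Protocol article*

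**What the plan says.** All references are to the protocol article.

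- **Response and model (Statistical analysis).** The text makes changes the analysed quantity, both for the seven diary variables and for the scales: "changes in ISI, GAD-7, PHQ-9, and QLQ-C30 scores, will be analyzed as quantitative data using mixed-effects models".
- **Missing data (Statistical analysis).** "Missing data will be handled using mixed-effects models under the missing-at-random assumption". Multiple imputation is mentioned only as a sensitivity analysis of the primary results.
- **Covariates (Statistical analysis).** The list names centre, TNM stage, treatment modalities, pain, menopausal status, baseline ISI severity and emergency medication. It is open-ended and its use is left to judgement. No baseline of GAD-7, PHQ-9, QLQ-C30 or any diary variable is named.
- **Visits (Secondary outcome; Table 1).** For GAD-7, "Evaluations will be conducted at Weeks 0 and 4". PHQ-9 and QLQ-C30 have the same two visits. ISI change is assessed at weeks 2, 4, 8 and 16, and the diary covers weeks 0 to 4.
- **Status.** The secondary outcomes are declared supportive and exploratory.

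**The concern.** A mixed model handles missing data by using a patient's other responses to inform the absent one. With a single change per patient there are no other responses. For GAD-7, PHQ-9 and QLQ-C30 the analysis is then a regression of change on treatment (plus any covariates used) among patients with a week-4 value, and the stated method does nothing for the rest.

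A change score without its own baseline as covariate is also usually less precise than a baseline-adjusted analysis, and it remains sensitive to chance baseline imbalance. It can be biased if dropout depends on baseline differently in the two arms. The week-0 values that would address all of this are already collected.

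**Working it through.** **1. The plan's own figure.** The only sample size is for the binary primary outcome. With 40.00% against 22.22%, two-sided α 0.05 and power 0.90, the unpooled formula gives

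n = (1.960 + 1.282)² × (0.40×0.60 + 0.2222×0.7778) / 0.1778² = 137.2,

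which matches the stated 137 per arm. Dropout: 137 / 0.85 = 161.2, hence 162. These figures do not bear on the secondary outcomes, except that they put the expected completers at 137 and the patients without week 4 at about 162 − 137 = 25 per arm. The article gives no SD or correlation for any scale.

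**2. Records per patient if the response is change.**

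| Outcome | Post-baseline values | Changes per patient |
|---|---|---|
| ISI | weeks 2, 4, 8, 16 | 4 |
| Diary variables | weeks 1, 2, 3, 4 | 4 |
| GAD-7, PHQ-9, QLQ-C30 | week 4 | 1 |

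Mixed-model handling therefore operates for ISI and the diary but not for the last row. In a simulated data set of 324 patients with 287 observed at week 4, a random-intercept model of change and ordinary regression gave the same treatment estimate (−0.303), because within-patient variance cannot be separated from the residual.

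**3. Precision.** Let the week-4 SD be 1, the baseline SD k, and their correlation r (k and r are assumptions).

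- Variance of change: 1 + k² − 2rk
- Residual variance after baseline adjustment (ANCOVA): 1 − r²
- Difference: (k − r)², which is never negative

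With k = 1 the ratio is (1 − r²) / [2(1 − r)] = (1 + r)/2. The detectable difference at 90% power with 137 per arm is (1.960 + 1.282) × √(2 × variance / 137).

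| r | Change | ANCOVA | Ratio | Detectable, change | Detectable, ANCOVA |
|---|---|---|---|---|---|
| 0.3 | 1.40 | 0.91 | 0.65 | 0.46 SD | 0.37 SD |
| 0.5 | 1.00 | 0.75 | 0.75 | 0.39 SD | 0.34 SD |
| 0.7 | 0.60 | 0.51 | 0.85 | 0.30 SD | 0.28 SD |
| 0.8 | 0.40 | 0.36 | 0.90 | 0.25 SD | 0.24 SD |

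With k = 0.7 and r = 0.5, the variance of change is 1 + 0.49 − 0.70 = 0.79 and the ratio is 0.75 / 0.79 = 0.95, a gain of about 5%.

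**4. Bias from dropout.** Simulation of 4,000 trials per setting: 162 per arm, no true effect, about 17% missing at week 4. In the differential setting, the log-odds of dropout rose by 1 per baseline SD in one arm and fell by 1 in the other, a deliberately strong contrast. Cells show mean estimate (empirical SE), in SD units.

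| r | Dropout mechanism | Change | ANCOVA | Two-visit model, unconstrained |
|---|---|---|---|---|
| 0.4 | same in both arms | 0.00 (0.130) | 0.00 (0.111) | 0.00 (0.129) |
| 0.4 | differs by arm | 0.181 (0.129) | 0.000 (0.111) | −0.001 (0.128) |
| 0.6 | same in both arms | 0.00 (0.108) | 0.00 (0.098) | 0.00 (0.106) |
| 0.6 | differs by arm | 0.125 (0.108) | 0.003 (0.098) | 0.003 (0.108) |

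The two-visit model simulated here let the baseline means differ by arm and estimated the difference in change. It removed the bias but gained almost no precision. The gain comes from adjusting for baseline, or from constraining the baseline means to be equal.

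**The case against.** The strongest reply is that one condensed sentence is being read as a full model specification. Much of that stands.

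- **All continuous outcomes unadjusted?** A reader might infer this, but the text does not support it. Baseline ISI severity is on the covariate list, so ISI change is not plainly without its baseline, although it is unclear whether it enters as a score or a category.
- **Other baselines excluded?** Also not supported. The list is open-ended, so they are unnamed rather than ruled out, and an analysis plan may add them.
- **Is the response certainly the computed change?** No. The text could mean weeks 0 and 4 both as responses, with change read from the group-by-week term. A patient without week 4 then still contributes. This reading is possible, but it is not the natural meaning of analysing changes.
- **Is the change analysis invalid?** No. It is valid in a randomised trial, and it was unbiased in the simulation when the dropout mechanism was the same in both arms. Differential dropout is an assumption. It is conceivable, since the arms use different needle lengths (1.5 mm and 0.3 mm), but nothing in the article shows it.
- **Is the precision gain secure?** Its size is not. It rests on an assumed correlation and SD ratio. The entry criterion of ISI ≥8 truncates that baseline and could shrink the gain for ISI.

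What remains is that the stated missing-data method does not act on three scales under the natural reading, and that a better use of data already in hand is not named.

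**Conclusion.** The point holds in a limited form and is minor. For the diary variables, GAD-7, PHQ-9 and QLQ-C30, the plan names change as the analysed quantity and no own baseline as covariate. For the three scales with a single post-baseline visit, the missing-at-random handling assigned to mixed models is empty if the response is the computed change, and no imputation is stated for them. It is not empty for ISI or the diary.

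Baseline adjustment would lower the variance by 15% to 35% for r between 0.7 and 0.3 with equal SDs, by about 5% in the less favourable case shown, and would not raise it apart from the negligible cost of one more parameter. It also removes bias from baseline-dependent dropout that differs by arm, provided that missingness depends only on variables in the model and that the baseline relation is correctly modelled. The primary outcome and the sample size are not affected.

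**What to change.** State the response variable and the baseline covariate for each continuous secondary outcome.

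- **GAD-7, PHQ-9, QLQ-C30:** ANCOVA of the week-4 score on treatment, own continuous baseline and centre. Alternatively, a constrained longitudinal model with weeks 0 and 4 both as responses and a common baseline mean across arms, which keeps patients without week 4 in the likelihood.
- **Diary variables and ISI:** a repeated-measures mixed model with treatment, week, treatment-by-week, centre and the outcome's own continuous baseline.

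Multiple imputation using the same covariates adds little beyond ANCOVA when only week 4 is missing, so it need not be required here.

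The cost is wording only. All baseline values are already scheduled, no visit or patient is added, and the text can be fixed before unblinding.

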### Exclusion criteria

(1) Those with severe heart, liver, kidney or other major diseases; (2) Those who are pregnant, lactating or planning to become pregnant within the next month; (3) Those with surgical plans during the trial period; (4) Those with a history of drug abuse or addiction; (5) Those who have taken sedative-hypnotic or antipsychotic drugs within two weeks before baseline, or have received other insomnia treatments (such as cognitive behavioral therapy, etc.) within three months before baseline; (6) Those with insomnia caused by cancer pain (NRS score≥4) or other physical diseases; (7) Those with mental or intellectual abnormalities who cannot finish the assessment; (8) Those who have long-term night work or irregular schedules; (9) Those who have received AA treatment within three months prior to enrollment; (10) Those with ulcers, abscesses, skin infections or other conditions at the treatment sites; (11) Those allergic to metals and adhesive tapes; (12) Those with ear deformities, perforations, cartilage deformations or other conditions; (13) Those with auricular cartilage inflammation or other serious complications related to the ear; (14) Those who have participated in other clinical medical trials within the past month.

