### Intervention

Throughout the study, all patients will receive the same standardized sleep hygiene education, which includes guidance on avoiding caffeine, tea, alcohol, and other stimulating beverages, maintaining regular daily schedules and appropriate sleep environments, and managing emotional well-being. Patients will be required to maintain a sleep diary for five weeks, documenting their sleep patterns at the following time points: week 0 - week 4.

All acupuncturists from the three centers will receive centralized standardized training before trial initiation, covering auricular point location, device application, insertion depth, disinfection procedures, patient instruction, and adverse event identification. Regular cross-center quality control meetings will be conducted to ensure protocol consistency.

Before home-based self-administration, participants will receive standardized training from trained acupuncturists, including face-to-face demonstration, video SOP instruction, and written operation manuals (**Supplementary Material 2**). During the first and fifth treatments, acupuncturists will verify participants’ ability to correctly locate auricular points, disinfect the auricle, apply the device, and perform pressing stimulation. During home treatment, participants will record device replacement and daily stimulation, upload operation photographs or videos weekly for researcher verification, and complete electronic adherence check-ins through WeChat. If incorrect operation or poor adherence is identified, researchers will provide timely guidance and retraining. A contact number will be provided for reporting adverse events (AEs) or operational problems.

If a patient experiences severe insomnia-related discomfort for two consecutive days or more, emergency medication usage may be used based on clinical need. The use of rescue medication is intended for short-term symptomatic relief and is not encouraged as routine treatment. Researchers will carefully record the name, dosage, frequency, and duration of medication use in the Case Report Form (CRF).

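### Emergency medication use is recorded only after randomisation and is itself a secondary outcome, so it should not be on the list of pre-specified covariates

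*Protocol article*

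**What the plan says.** All places are in the protocol article.

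- **Statistical analysis, last sentence.** Study center, TNM stage, cancer treatment modalities, pain level and menopausal status are listed, followed by "baseline ISI severity, and emergency medication usage, will be considered as pre-specified covariates where appropriate". The sentence is tied to no particular model.
- **Statistical analysis, same paragraph.** Rescue use is also an outcome: "Secondary outcomes, including treatment response rate, treatment remission rate, and emergency medication usage, will be analyzed as qualitative data with repeated measures", by generalized estimating equations. For the primary outcome: "The primary outcome, the treatment response rate at week 4, will be compared using the Cochran-Mantel-Haenszel test". No strata are named.
- **Secondary outcome.** "Emergency medication usage: The percentage of patients using emergency medication usage", with dose, frequency and duration, "will be recorded at weeks 1, 2, 3, 4, 8, and 16". Table 1 agrees. It puts randomisation at week 0 and schedules no baseline value for rescue use.
- **Intervention.** The trigger is "If a patient experiences severe insomnia-related discomfort for two consecutive days or more, emergency medication usage may be used based on clinical need".
- **Exclusion criteria, item 5.** Excluded are "Those who have taken sedative-hypnotic or antipsychotic drugs within two weeks before baseline".

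**The concern.** A covariate in a randomised comparison should be fixed before treatment can influence it. Rescue use is not. It starts after allocation, and it is prompted by the symptom that the intervention is meant to relieve. By making it an efficacy outcome, the protocol itself allows that treatment may change it.

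Conditioning on such a variable does two things. It compares the arms within subgroups that randomisation no longer balances: if AA reduces the need for rescue, the AA patients who still use it are, on average, a more severe group than the NAA patients who use it. It also holds constant something that treatment may have altered. Either way, the coefficient for treatment need not be the overall AA versus NAA effect that the trial sets out to assess.

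At stake are the models for response, remission, ISI change and the sleep diary and, if rescue use became a stratum, the primary test.

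**Working it through.** **1. Can the covariate be read as a baseline value?** No. Recording starts at week 1, after randomisation at week 0. Recent sedative-hypnotic users are excluded, so a baseline version would be close to constant. In the same list ISI is expressly labelled as baseline and rescue use is not.

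**2. The plan's own sample size.** Inputs from the Sample size section: response 40.00% and 22.22%; "A bilateral significance level (α) of 0.05 and a statistical power (1-β) of 0.9 were established"; 137 per arm; 15% dropout. The unpooled two-proportion formula gives

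n = (1.960 + 1.282)² × (0.40×0.60 + 0.2222×0.7778) / (0.40 − 0.2222)² = 137.2 per arm,

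which matches the stated 137. Then 137/0.85 = 161.2, rounded up to 162 per arm, 324 in total. The sample size is not in question. The planned risk difference is 0.400 − 0.222 = 0.178.

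**3. A worked example by hand (assumed inputs).** Rescue use 10% in AA and 30% in NAA; response 43% vs 28% without rescue and 13% vs 9% with rescue.

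- AA overall: 0.9×0.43 + 0.1×0.13 = 0.400
- NAA overall: 0.7×0.28 + 0.3×0.09 = 0.223
- Crude risk difference: 0.177
- Mantel-Haenszel weights: 0.9×0.7/1.6 = 0.394 (no rescue) and 0.1×0.3/0.4 = 0.075 (rescue)
- Stratified risk difference: (0.394×0.15 + 0.075×0.04)/(0.394 + 0.075) = 0.132

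The overall response rates are essentially the planned ones, yet stratifying on rescue use lowers the estimate from 17.7 to 13.2 percentage points.

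**4. Simulation over a range (assumed inputs).** There were 4,000 trials per scenario at 137 per arm, with the planned response rates. Rescue use and non-response were linked by a latent correlation of 0.3, 0.5 or 0.7. An unstratified Mantel-Haenszel test was compared with one stratified on rescue use. The unstratified results were a risk difference of 0.177 to 0.179 and power of 0.89 to 0.90 throughout. In the table, values run from correlation 0.3 to 0.7.

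| Rescue use, NAA vs AA | Stratified risk difference | Stratified power | No effect on response: stratified difference | No effect: rejection rate |
|---|---|---|---|---|
| 30% vs 30% | 0.177 to 0.180 | 0.91 to 0.94 | about 0 | about 0.05 |
| 30% vs 20% | 0.163 to 0.144 | 0.84 to 0.78 | −0.014 to −0.026 | 0.058 to 0.088 |
| 30% vs 15% | 0.153 to 0.127 | 0.78 to 0.66 | −0.021 to −0.042 | 0.071 to 0.134 |
| 40% vs 20% | 0.145 to 0.105 | 0.73 to 0.50 | −0.027 to −0.059 | 0.082 to 0.222 |

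A smaller gap matters less. With 15% in NAA vs 10% in AA, correlation 0.3 and all 162 per arm analysed, the stratified risk difference was 0.170 and power about 0.91, against 0.94 unstratified.

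Negative values favour NAA. The stratified test stands in for any adjusted efficacy model; the GEE and mixed models were not simulated.

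**The case against.** **The list is hedged and tied to no model.** This is true, and it limits the reach of the point. A reader might infer that the primary test will be stratified on rescue use. The article does not say so: it names no strata, and the covariate sentence stands apart from the sentence on the primary test. The exposure that can be claimed is to the secondary models, which the article calls supportive and exploratory, and to the primary test only conditionally. The hedge does not cure the item, because rescue use is not a suitable adjustment variable in any of the efficacy comparisons of the overall effect.

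**The statistical analysis plan may settle it.** It may. But the point is not that something was left out. The article names an unsuitable covariate, and a plan that followed it would carry it over.

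**The bias is not inevitable.** This stands. With equal rescue use by arm, the simulations show none, and with a small gap it is modest. The documents give no rescue rates, so nobody can say which row of the table applies.

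**This is not a route to a false claim for AA.** This also stands, under the assumptions used. A reader might take the raised rejection rate to mean that adjustment could manufacture a benefit of AA. In every null scenario with unequal rescue use, the spurious difference favoured NAA. The scenarios treat rescue use as a marker of severity. Rescue drugs also relieve symptoms, and that path can pull the other way, so the documents do not fix the direction.

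**Rescue use would not be regressed on itself.** Agreed. The hedge plausibly excludes it from the model in which it is the outcome, so that overlap is not pressed as a separate error.

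**Conclusion.** The covariate list is wrong as written on one item. Four facts establish this without any calculation: rescue use is recorded only after randomisation, it is prompted by the symptom under treatment, a baseline reading is untenable, and it is analysed as an outcome in the same paragraph. An efficacy model that conditions on it need not estimate the overall randomised effect.

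The size cannot be derived from the article. Under assumed rescue rates and correlations it runs from no bias (equal use by arm) through a slight loss (risk difference about 0.17) to a severe one (0.105, with power 0.50 at 137 per arm). With no true effect on response and lower rescue use in AA, rejection is about 0.06 to 0.22 instead of 0.05, in favour of NAA. These figures are illustrations of a stratified test that the article does not specify, and not forecasts for this trial.

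**What to change.** 1. Delete emergency medication usage from the covariate list in Statistical analysis.
2. State that covariates are restricted to variables fixed at or before randomisation, with pain level and cancer treatment modalities taken at their baseline values.
3. Keep rescue use as a secondary outcome, analysed as already planned.

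Optional: one pre-specified sensitivity analysis of how rescue use affects the primary result, for example counting patients with any rescue use up to week 4 as non-responders. That is one choice among several, and the correction does not depend on it.

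The cost is one or two sentences in the protocol or statistical analysis plan, made before unblinding, plus one table if the optional analysis is added. No new data are needed and the sample size does not change.

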**Figure 1 f1:**
[figure not shown]
Trial flow chart. ISI, Insomnia Severity Index; GAD-7, Generalized Anxiety Disorder Scale-7; PHQ-9, Patient HealthQuestionnaire-9; QLQ-C30, Quality of Life Core Scale-30.

**Table 1 T1:** Schedule of enrolment, interventions and assessment times.

Study period	Enrolment		Intervention period				Follow-up period	
Time point	Week -1	Week 0	Week 1	Week 2	Week 3	Week 4	Week 8	Week 16
Eligibility screen	**×**							
Sign informed consent	**×**							
randomization		**×**						
Interventions								
Auricular acupuncture								
Nonspecific auricular acupuncture								
Primary outcomes								
Treatment response rate						**×**		
Secondary outcomes								
Treatment remission rate				**×**		**×**	**×**	**×**
Treatment response rate				**×**			**×**	**×**
Change in ISI score				**×**		**×**	**×**	**×**
Sleep diary								
GAD-7		**×**				**×**		
PHQ-9		**×**				**×**		
QLQ-C30		**×**				**×**		
Adverse events			**×**	**×**	**×**	**×**		
Emergency medication usage			**×**	**×**	**×**	**×**	**×**	**×**
Success of blinding						**×**		

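### Emergency medication usage, measured only after randomisation and itself a secondary outcome, is listed as a covariate; adjusting efficacy comparisons for it can bias the effect in either direction

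*Protocol article*

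**What the plan says.** All references are to the protocol article.

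- **Statistical analysis, covariates.** The list names centre, TNM stage, cancer treatment modalities, pain level and menopausal status, and closes with "baseline ISI severity, and emergency medication usage, will be considered as pre-specified covariates where appropriate". It does not say which models the list serves, and the primary Cochran-Mantel-Haenszel (CMH) test is given no strata.
- **Statistical analysis, outcomes.** The same section makes it an outcome, fitted by generalized estimating equations (GEE): "Secondary outcomes, including treatment response rate, treatment remission rate, and emergency medication usage, will be analyzed as qualitative data with repeated measures". Sleep-diary, ISI, GAD-7, PHQ-9 and QLQ-C30 changes "will be analyzed as quantitative data using mixed-effects models".
- **Secondary outcome.** The percentage of users, with dose, frequency and duration, "will be recorded at weeks 1, 2, 3, 4, 8, and 16".
- **Table 1.** Randomisation is at week 0. The row "Emergency medication usage" has its first mark at week 1.
- **Exclusion criteria.** Excluded are "Those who have taken sedative-hypnotic or antipsychotic drugs within two weeks before baseline".
- **Intervention.** The trigger is "severe insomnia-related discomfort for two consecutive days or more, emergency medication usage may be used based on clinical need".

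**The concern.** The other listed variables can be fixed at or before randomisation. Emergency medication usage cannot. Table 1 and the outcome section give it no baseline value, and the exclusion of recent sedative-hypnotic users prevents reading it as baseline hypnotic use. Its trigger is the symptom that the assigned treatment is meant to relieve, so it is partly a result of treatment and shares causes with the ISI outcome.

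Conditioning on such a variable compares AA users with NAA users, and AA non-users with NAA non-users. Randomisation did not create those subgroups. If AA works, lowers rescue use, and users do worse, adjustment removes part of AA's own benefit. If the rescue drug itself lowers ISI, adjustment can raise the estimate instead. The protocol gives neither the rescue rate by arm nor the outcome of users, so the direction cannot be known in advance.

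**Working it through.** **1. Plan's own figure.** Inputs from the Sample size section: 0.40 versus 0.2222, two-sided 0.05, power 0.90. The unpooled formula gives n = (0.40×0.60 + 0.2222×0.7778) × (1.960 + 1.282)² / 0.1778² = 137.2 per group, against 137 stated. Then 137/0.85 = 161.2, rounded up to 162. Both reproduce. The concern does not depend on them; 137 per arm is used below.

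**2. Response stratified by any rescue use (yes/no).** Let u be the rescue rate in an arm, r the response among users and p the response in the whole arm.

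- Non-user response = (p - u·r)/(1 - u).
- Mantel-Haenszel weights: uA·uN/(uA + uN) for users; (1 - uA)(1 - uN)/[(1 - uA) + (1 - uN)] for non-users.

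All values of u and r are assumptions.

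*No true difference: p = 30% in both arms, r = 10% in both.* Worked case, 10% AA versus 20% NAA: non-users respond at 0.3222 versus 0.3500 and users do not differ. The weights are 0.0667 and 0.4235. The difference is 0.4235 × (-0.0278)/0.4902 = -0.024.

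Rejections come from 400,000 simulated trials per row, two-sided 0.05 CMH test without continuity correction:

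| Rescue use, AA / NAA | Stratified difference (points) | Rejects against AA | Rejects for AA |
|---|---|---|---|
| 20% / 20% | 0 | 2.5% | 2.5% |
| 5% / 10% | -1.1 | 3.9% | 1.6% |
| 10% / 20% | -2.4 | 6.3% | 0.8% |
| 10% / 30% | -5.3 | 15.4% | 0.2% |
| 30% / 10% | +5.3 | 0.2% | 15.6% |

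Without stratification by rescue, rejections are 2.4 to 2.5% each way in every row.

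*Planned effect: p = 40.00% versus 22.22%, r = 20% in AA and 10% in NAA.*

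| Rescue use, AA / NAA | Stratified difference (points) |
|---|---|
| 15% / 15% | 17.8 |
| 5% / 10% | 17.0 |
| 10% / 20% | 16.0 |
| 20% / 10% | 19.9 |

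In the 10% / 20% row, power falls from about 89% to about 82%.

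**3. ISI change in a linear model.** If users improve b points less than non-users in both arms, adjustment moves the arm difference by b × (uN - uA). For b = 2 to 4 this is 0.1 to 0.2 ISI points at 5% / 10% use, 0.2 to 0.4 at 10% / 20%, 0.4 to 0.8 at 10% / 30%, and 0 at equal use.

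**4. Direction.** A separate large-sample simulation (4 million patients, assumed logistic models, rescue use about 8 to 13% in AA and 20 to 25% in NAA) compared unadjusted with rescue-stratified risk differences:

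- Rescue use goes with non-response: 0.153 falls to 0.133.
- The rescue drug raises response: 0.115 rises to 0.146.
- No treatment effect on response, with an unmeasured severity factor driving both rescue use and response: 0.000 becomes -0.021.

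**The case against.** The strongest reply is that the sentence orders nothing. Covariates are only to be considered where appropriate, no model is named, and assigning covariates to models is normal work for a statistical analysis plan. The sentence directly follows the one on multiple imputation, where rescue use would be a legitimate auxiliary variable. The larger numbers describe a CMH test stratified by rescue, which the protocol does not specify. In the mixed models, where the list fits more naturally, the shift at 5% / 10% and 10% / 20% use is only 0.1 to 0.4 ISI points, small beside the 8-point response definition, and those outcomes are declared supportive and exploratory. The rows with the highest error rates also need rescue use to differ threefold while AA has no effect on response, which is strained in a trial with blinded patients.

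Much of this stands as a limit on size. The 15% rejection rates are extreme cases and should not be read as expected ones. It does not remove the point. The qualifier neither makes the variable a baseline one nor keeps it out of the efficacy models. Nor is this a gap left for a later document: the protocol affirmatively names an unsuitable variable as pre-specified, so an analysis plan would have to repeat the error or depart from the protocol. The imputation reading is acceptable, and the fix preserves it.

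**Conclusion.** The concern holds. Three facts are plain in the text: emergency medication usage is recorded only after randomisation, it is a secondary outcome, and it is listed as a covariate. Adjusting an efficacy comparison for it can move the estimate up or down.

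The size cannot be fixed from the documents. Under the assumed inputs it runs from nil at equal use, through 1 to 2 percentage points of response at 5% / 10% or 10% / 20% use, to about 5 points in the extreme 10% / 30% case. Bias in the primary week-4 comparison is possible rather than certain, because the text allows adjustment there without requiring it. The point should be corrected, but it does not invalidate the design.

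**What to change.** Remove emergency medication usage from the covariate list for all between-group efficacy analyses and keep it as the planned secondary outcome. Suggested wording:

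> Adjustment covariates are limited to values recorded at baseline: centre, ISI severity, TNM stage, menopausal status, pain level and cancer treatment modalities. Emergency medication usage will not serve as a covariate or stratum in any between-group efficacy analysis; it may be used only as an auxiliary variable in the multiple-imputation model.

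This does not prevent a labelled sensitivity analysis that counts rescue users as non-responders, since that changes the definition of response and does not condition on rescue use.

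The cost is one sentence in the Statistical analysis section. No new data are needed, and sample size and access to rescue medication are unchanged. Any imbalance in rescue use will still show in its own outcome analysis.
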